### Study measures

Study participants will complete the following instruments as part of a paper-and-pencil battery of measures (see Table 3):*Sociodemographic-clinical questionnaire*. The following information will be collected: gender, age, ethnic group, marital status, living arrangements, educational level, employment status, and annual income. Relevant clinical variables, such as family and personal medical history, years of FMS diagnosis and comorbid conditions will also be assessed.

**Table 3 Tab3:** Study periods at which measures and data are collected

Study measures	Baseline	During treatment	2 months	12-months
Demographic information (gender, age, etc.)	X			
History of FMS (years of illness)	X			
Contact details	X			
SCID-I (depression module)	X			
*Screening measures*				
MMSE (cognitive impairment)	X			
*Primary outcome measure*				
FIQR (functional impairment)	X		X	X
*Secondary outcome measures*				
FSDC (fibromyalginess)	X		X	X
HADS (anxiety and depression)	X		X	X
PSS-10 (perceived stress)	X		X	X
MISCI (subjective cognitive impairment)	X		X	X
EQ-5D-5L (quality of life)	X			X
CSRI (health economic evaluation)	X			X
FFMQ^a^ (mindfulness facets)	X		X	X
PCS^a^ (pain catastrophizing)	X		X	X
PIPS^a^ (psychological inflexibility)	X		X	X
SCS-12^a^ (self-compassion)	X		X	X
*Other measures*				
Structural + Functional Neuroimaging data	X		X	
Inflammatory data	X		X	
CEQ (Expectation/Satisfaction with treatment)	X (EXP)		X (SAT)	
PGIC & PSIC (Impression of change)			X	X
Treatment attendance form: Attendance at each scheduled MBSR/FibroQoL session		X		
Log of MBSR and FibroQoL practices		X		
Treatment fidelity (review of video-taped MBSR sessions) & monitoring of adverse events		X	X	X

*CEQ* Credibility/Expectancy Questionnaire, *CSRI* Client Service Receipt Inventory, *EQ-5D-5L* EuroQoL questionnaire, *FFMQ* Five Facet Mindfulness Questionnaire, *FIQR* Revised Fibromyalgia Impact Questionnaire, *FSDC* Fibromyalgia Survey Diagnostic Criteria, *HADS* Hospital Anxiety and Depression Scale, *MISCI* Multidimensional Inventory of Subjective Cognitive Impairment, *MMSE* Mini-Mental State Examination, *PCS* Pain Catastrophizing Scale, *PGIC & PSIC* Patient Global and Specific Impression of Change, respectively, *PIPS* Psychological Inflexibility in Pain Scale, *PSS-10* Perceived Stress Scale, *SCID-I* Structured Clinical Interview for DSM Axis I Disorders, *SCS-12* Self-Compassion Scale

^a^Secondary outcome measures that also considered process variables

Inflammatory data = Cytokines Th1: IL-6, IL-8; cytokines Th2: IL-10; + high-sensitivity CRP test

Structural and Functional Neuroimaging = Voxel-Based Morphometry, Diffusion Tensor Imaging, pCASL, and rs-fMRI

#### Clinical characteristics and screening measures

The *Mini-Mental State Examination* (MMSE) [53, 54] is a 30-item questionnaire designed to measure cognitive impairment that is widely used in older adults. The MMSE includes tests for orientation, memory, concentration, and visuospatial ability. In non-geriatric populations (≤65 years), such as our study sample, the threshold that suggests a “probable case” of cognitive impairment when the score is less than 27 points.The *Structured Clinical Interview for DSM Axis I Disorders* (SCID-I) [55]. Clinical diagnosis of mood disorders according to DSM-IV diagnostic criteria will be confirmed using the research version of the SCID-I (mood disorders module).

#### Primary outcome measure

The *Revised Fibromyalgia Impact Questionnaire* (FIQR) [56, 57] includes 21 individual items that are all answered on an 11-point numeric rating scale from 0 to 10, with 10 reflecting greater impairment. The time frame is the previous 7 days and the items are distributed into three associated domains: “physical function” (9 items); “overall impact” (2 items that address the overall impact of FM on functioning and symptom severity); and “severity of symptoms” (10 items; pain, energy, stiffness, quality of sleep, depression, memory problems, anxiety, tenderness to touch, balance problems, and sensitivity to loud noises, bright lights, odours, and cold temperatures). The scoring system is straightforward: the physical function domain (0 to 90) is divided by 3, the overall impact domain (0 to 20) is not transformed, and the severity of symptoms domain (0 to 100) is divided by 2. The FIQR total score (0 to 100) is obtained by adding the three domain scores. The FIQR has been shown to be a psychometrically sound instrument, is clinically useful as it can be completed by patients in less than 2 min and scored in approximately 1 min, is recommended as a primary efficacy endpoint measure in FMS clinical trials, and is the “gold standard” assessment measure for multidimensional functional status in FMS patients [58].

#### Secondary outcome measures and process measures

The *Fibromyalgia Survey Diagnostic Criteria* (FSDC) [59, 60] is a 6-item self-report questionnaire that registers the key symptoms of FMS according to the latest revision of the ACR. It includes assessment through the Widespread Pain Index (WPI) identifying 19 body areas (jaws, shoulders, upper arms, lower arms, hips, upper legs, lower legs, neck, chest, upper back, lower back and abdomen) where pain or tenderness was felt during the previous 7 days (total score 0–19). The Symptom Severity Scale (SS; range from 0–12) includes three major symptoms (fatigue, trouble thinking/remembering and waking up tired or unrefreshed), which is scored from 0 to 3, as well as three additional symptoms (pain or cramps in lower abdomen, depression, headache), which can be coded as present (1) or absent (0). The fibromyalgianess scale is defined as the sum of the WPI items (0–19) and the 6-item SS scale (0–12), so total scores can range from 0 to 31.The *Client Service Receipt Inventory* (CSRI) [61, 62] used for the present project will be designed to collect retrospective data on medication and service receipt: 1. Medication. A profile of the patient’s use of all prescribed medications (analgesics, non-steroidal anti-inflammatories, short- and long-acting opioids, etc.) will be requested, including the name of the drug, the prescriber, the dosage level, the total number of days taking the drug, the total dosage consumed, the reasons for changing the drug, and adherence. 2. Service receipt. We will collect information about emergency services, general medical in-patient hospital admissions and out-patient health care services. Patients will also be asked about type and number of diagnostic tests administered. As shown in Table 3, the CSRI will be administered at baseline and at a 12-month follow-up*; on both occasions, the previous 12 months will be reviewed*.The *EuroQoL-5D questionnaire* (EQ-5D-5L) [63] is a widely used health-related quality of life instrument with a non-disease-specific classification system composed of 2 parts: Part 1 is a self-reported description of health problems classified into five dimensions. Patients mark one of five degrees of severity in each dimension. The time frame is the day of responding. Part 2 records the current subject’s health on a Visual Analogue Scale (VAS); a vertical 10 cm line on which the best and worst imaginable health states score 100 and 0, respectively.The *Hospital Anxiety and Depression Scale* (HADS) [64, 65] was originally developed to quantify the severity of anxiety and depressive symptoms in non-psychiatric hospital patients The HADS includes a total of 14 items that assess anxiety (HADS-A) and depressive (HADS-D) symptoms, with 7 items in each subscale. Each item is answered on a four-point (0-to-3) scale so that possible scores range from 0 to 21 for both anxiety and depressive symptoms, with higher scores indicating greater severity.The *Perceived Stress Scale* (PSS-10) [66] is a 10-item, self-administered instrument that measures the degree to which situations in one’s life are considered stressful. Scores range from 0 to 72. The Spanish version of the PSS-10 has adequate reliability and validity [67].The *Multidimensional Inventory of Subjective Cognitive Impairment* (MISCI) [68] is a 10-item measure of perception of cognitive dysfunction in FMS, developed through classical test theory and item response theory from cognitive functioning item banks that were developed as part of the Patient Reported Outcomes Measurement Information System (PROMIS). The MISCI showed excellent internal reliability, low ceiling/floor effects, and good convergent validity with a similar measure.The *Pain Catastrophising Scale* (PCS) [69, 70] is a 13-item questionnaire derived partially from the Coping Strategies Questionnaire and other descriptions of catastrophising. It has three dimensions: Rumination (tendency to focus excessively on pain sensations), Magnification (tendency to magnify the threat value of pain sensations) and Helplessness (tendency to perceive oneself as unable to control the intensity of pain). The PCS total score and subscale scores are computed as the algebraic sum of ratings made for each item. PCS items are rated in relation to frequency of occurrence on 5-point scales (0 = never ~ 4 = almost always).The *Five Facet Mindfulness Questionnaire* (FFMQ) [71, 72] consists of 39 items that assess five facets of mindfulness. Items are rated on a Likert scale ranging from 1 (never or very rarely true) to 5 (very often or always true). The factors include: *Observing*, including noticing or attending to internal and external experiences such as sensations, thoughts, or emotions. *Describing* refers to labelling internal experiences with words. *Acting with awareness* involves focusing on one’s activities in the here and now as opposed to behaving mechanically. *Non-judging of inner experience* refers to taking a non-evaluative stance toward thoughts and feelings. Finally, *non-reactivity to inner experience* is allowing thoughts and feelings to come and go, without getting caught up in or carried away by them. In a recent online survey answered by 4,986 FMS patients from all 50 US states and 30 countries, the FFMQ subscales was shown to discriminate well among FMS patients self-identified as meditators or non-meditators. Overall, FMS patients with higher mindfulness scores had lower levels of FMS symptom severity as measured with the FIQR [73].The *Self-Compassion Scale-short form* (SCS-12) [74, 75] is a shorter version (12 items) of the SCS (26 items). The SCS was designed to assess overall self-compassion (total score) and components of self-compassion across three dimensions: common humanity, mindfulness and self-kindness. The SCS–SF shows good internal consistency (Cronbach’s α ≥0.86) and very high convergence with the long form of the scale (r ≥0.97).The *Psychological inflexibility in pain scale* (PIPS) [76, 77] is a 12-item scale designed to measure psychological inflexibility in pain patients. The instrument includes two factors: *avoidance* and *cognitive fusion* related to pain. The items consist of different statements that are considered to be related to chronic pain, psychological inflexibility, suffering and disability (coherent with the ACT theory). All the items are rated on a 7-point Likert-type scale that ranges from “1 = never true” to “7 = always true”, with higher scores indicating more psychological inflexibility.

#### Other measures

The *Patient Global Impression of Change (PGIC) and Pain Specific Impression of Change* (PSIC) [78] are measures that have been frequently used as indicators of meaningful overall change [on a 7-point Likert scale, from 1 = “Much better” to 7 = “Much worse”] in treatments for chronic pain, whereas the PSIC asks about the impression of change in more specific domains: physical and social functioning, work-related activities, mood, and pain.*Adapted version of the Credibility/Expectancy questionnaire* (CEQ) [79]. The CEQ is a 6-item questionnaire for measuring treatment expectancy and credibility for use in clinical outcome studies. The questionnaire shows overall high internal consistency (α = 0.84–0.85). We will use an adapted version that evaluates Expectancy (at the end of the first treatment session) and Opinion (at the end of the last treatment session) about MBSR and FibroQoL.*Log of out-session for MBSR and psychotherapeutic practices*. An *ad hoc* instrument for the weekly recording of formal and informal mindfulness or FibroQoL home practice. A recent systematic review of systematic reviews and a meta-analysis of standardised mindfulness interventions (MBSR and MBCT) indicated that an increase in total minutes of mindfulness practice and class attendance are associated with a reduction of stress and mood complaints [80].*Adverse events of the interventions. Ad hoc* measure to check for adverse events (e.g., anxiety, dizziness, sleep problems, etc.) across the interventions and follow-up.

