## Background

Fibromyalgia (FMS) is a debilitating syndrome usually diagnosed in women between the ages of 20 and 50 years [1]. It is characterised by multifocal pain, fatigue, disturbed sleep, cognitive problems, and high levels of distress [2]. A survey performed in five European countries indicated that the estimated overall prevalence of FMS is 2.9 % in the general population [3]. Patients with FMS typically present comorbidities with psychiatric disorders such as anxiety (13–63.8 %) and depressive disorders (20–80 %) [4]. In addition, FMS is associated with high direct (medical visits, multiple prescriptions of medications, etc.) and indirect (absenteeism, work loss, etc.) costs in industrialised countries [5]. Among chronic pain conditions, FMS causes the highest rates of unemployment, the highest rate of incapacity benefits claim rate, and the greatest number of days absent from work [6]. FMS represents a great challenge for health professionals because of the lack of optimal treatment options. The effectiveness of pharmacological interventions is generally limited and more ubiquitous effects have been found for non-pharmacological treatments [7].

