#### Analysis of clinical efficacy

To assess treatment effects, we will perform Intention-to-Treat analyses, which will include all participants who undergo random allocation, using multiple imputation to replace missing values.

To study the differences in the primary outcome and in each of the secondary outcomes between groups, linear mixed-effects models [85] will be prepared using Restricted Maximum Likelihood to estimate the parameters. Comparisons amongst treatment groups at post-treatment and at 12-month follow-up will be computed with estimates derived from the linear mixed-effect models (use of the Bonferroni method to adjust the significance level of the pairwise contrasts). Calculations of between-groups effect sizes using Cohen’s *d* with its 95 % confidence interval will be based on the pooled standard deviation at baseline. Finally, to make the findings from the present RCT meaningful to clinicians, the number-needed-to-treat (NNT) [86] in the MBSR condition will be reported. Taking the Luciano et al. [87] NNT approach as our reference, we dichotomise participants into responders or non-responders using three separate cut-off criteria: (a) ≥ 20 % reduction on the FIQR total score from baseline to post-treatment; (b) ≥ 50 % reduction on the FIQR total score from baseline to post-treatment; and (c) number of patients crossing a cut-off point (reaching no worse than mild functional impairment; FIQR total score < 39).

Given that some pharmacological treatments may interfere with cytokine levels [88], differences in cytokine levels between patients taking vs. not taking antidepressants will be evaluated.

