## Discussion

The study described here will evaluate, for the first time, the cost-utility of MBSR for FMS patients compared with usual care and with an empirically-validated intervention (FibroQol) which proved to be cost-effective in such patients in a high-quality RCT [41]. Therefore, this is a 3-armed RCT in which we include an active control condition (psycho-education) that permits us to control the “frustrebo response” (disappointment among control participants at not receiving treatment) associated with waiting-list and TAU conditions [92]. The RCT was designed following the CONSORT recommendations, the economic evaluation was planned following the updated ISPOR core recommendations for cost-effectiveness analyses alongside RCTs, the sample size in each study arm is sufficiently large and the follow-up period is sufficiently long to capture important costs and outcomes. If our trial results are sufficiently robust, MBSR programmes might be delivered as part of a strategic, coherent or appropriately resourced approach for patients with FMS in the healthcare context [80, 93]. According to Gotlink et al. [80], “*further research should also look more into the mechanisms whereby these therapies (MBSR-MBCT) are efficacious*”. In the present RCT, we are not only interested in the clinical effects of MBSR at long-term, but also in the “process” psychological variables and neurobiological changes that contribute to them, which is a current source of interest and debate in the scientific literature [89, 94].

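### The adverse-event measure has no baseline although two of its three named events are features of fibromyalgia, and it is unclear whether TAU patients are asked

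*Protocol article*

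**What the plan says.** The Protocol article (Other measures) has an item titled "Adverse events of the interventions", described as an ad hoc "measure to check for adverse events (e.g., anxiety, dizziness, sleep problems, etc.) across the interventions and follow-up".

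The timing is in Table 3 (Study measures), in a combined row: "Treatment fidelity (review of video-taped MBSR sessions) & monitoring of adverse events". It is marked during treatment, at 2 months and at 12 months. The baseline cell is empty.

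The Background says of the disease: "It is characterised by multifocal pain, fatigue, disturbed sleep, cognitive problems, and high levels of distress". It also gives comorbid anxiety disorders as 13 to 63.8 %. The FIQR symptom items (Primary outcome measure) include "quality of sleep, depression, memory problems, anxiety, tenderness to touch, balance problems".

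Three other instruments bear on worsening. FIQR and HADS are taken at baseline, 2 months and 12 months. PGIC is taken at 2 and 12 months on a scale running to much worse. Under Analysis of clinical efficacy, primary and secondary outcomes are compared between all arms by mixed models. The responder rules there count improvement, such as a set percentage "reduction on the FIQR total score from baseline to post-treatment", or reaching a FIQR total below 39.

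**The concern.** Many patients will enter with poor sleep or anxiety. If such a patient reports either one on the adverse-event measure at 2 months, nothing on that measure shows whether it began during the trial, worsened, or was there all along. The harms table would then mix background disease with any effect of the programmes.

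A second doubt is who is asked, and how often. The item's title and its shared row with MBSR fidelity review leave open whether TAU patients complete it. The only other Table 3 rows marked during treatment are the session attendance form and the practice log, which belong to the group programmes. If the group arms are questioned on occasions when TAU is not, background symptoms alone could produce a difference against TAU.

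At stake is how well the trial can describe the safety of MBSR. A later analysis plan can define events and add tables, but it cannot recover a baseline checklist that was never given.

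**Working it through.** The protocol gives no figure for adverse events, so there is none to reproduce. The check has three parts.

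**1. Named events against the protocol's own account of the disease**
- Sleep problems: disturbed sleep is a defining feature in the Background, and sleep quality is a FIQR item. Overlap.
- Anxiety: a FIQR item and a common comorbidity (13 to 63.8 %). Overlap.
- Dizziness: not listed as a symptom. The nearest FIQR item is balance problems, which is not the same. Overlap not shown.

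So the overlap is established for two of three.

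**2. What the missing baseline costs if all arms are asked alike**

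Inputs from the protocol: n = 60 per arm (Participants). Background prevalence b is taken across the Background's anxiety range as a stand-in, since those figures are for anxiety disorders and not for reports on this form.

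Assumptions: among patients free of the symptom at entry, new onset is 5 % in control and 20 % in MBSR; existing symptoms persist and are reported equally in both arms; two-sided alpha is 0.05.

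- Without a baseline, any symptom present counts: p = b + (1 − b) × onset.
- With a baseline, only new onset counts: q = (1 − b) × onset.
- Power = Φ[(difference − 1.96 × SE0) / SE1], with SE0 from the pooled proportion and SE1 from the separate proportions.

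Worked at b = 0.13:
- Without baseline: 0.13 + 0.87 × 0.05 = 0.174 against 0.13 + 0.87 × 0.20 = 0.304. Difference 0.131, SE0 = 0.0778, SE1 = 0.0769, power 0.39.
- With baseline: 0.87 × 0.05 = 0.044 against 0.87 × 0.20 = 0.174. Difference again 0.131, SE0 = 0.0568, SE1 = 0.0556, power 0.63.

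| Background b | Difference (points) | Power, no baseline | Power, with baseline |
|---|---|---|---|
| 13 % | 13.1 | 0.39 | 0.63 |
| 20 % | 12.0 | 0.30 | 0.59 |
| 40 % | 9.0 | 0.16 | 0.46 |
| 63.8 % | 5.4 | 0.09 | 0.30 |

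The expected difference is the same under both ways of counting, so the loss is in precision and there is no bias. The last row is rough, because only 60 × 0.018 = 1.1 new events are expected in control.

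**3. Unequal questioning against TAU**

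Table 3 has one mark in the during-treatment column and gives no frequency. Suppose a background symptom is reported with probability p = 0.10 at each enquiry and no programme causes harm. Suppose also that TAU is asked only at 2 and 12 months, and the group arms have m further in-treatment enquiries.
- Independent reports: P(at least one) = 1 − (1 − p)^k. TAU, k = 2: 0.190. Group arms, m = 1, k = 3: 0.271, a gap of 8 points. Group arms, m = 8, k = 10: 0.651, a gap of 46 points.
- Fully persistent symptoms: P(at least one) = p for any k, so 10 % against 10 % and a gap of zero.
- TAU not asked at all: no comparison with TAU is possible.

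Long-standing symptoms lie nearer the persistent case. The 46-point figure is an extreme corner, and the protocol gives neither p nor m.

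**The case against.** The strongest reply is that the protocol already measures worsening. FIQR, with its sleep, anxiety and balance items, and HADS have baselines and are compared between all arms by models that detect change in either direction. PGIC records global worsening. This stands as a substantial mitigation, but a partial one. These scales do not tell whether a given adverse-event report is new, and the FIQR's 7-day window at 2 and 12 months misses transient problems during treatment.

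A second reply is that the form is not shown. It may ask about new or intervention-related problems, for which an empty baseline cell is usual. Item wording and event definitions are commonly left to fuller documents, and their absence is not held against the article. But the stated schedule would still leave no baseline record to check such reports against, and TAU patients would have no programme to attribute them to.

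A reader might infer more than the documents support:
- That harm cannot be separated from disease or compared between arms at all. The scales above, and randomisation with equal questioning, contradict this.
- That MBSR and FibroQoL cannot be compared on safety. The note to Table 2 calls the programmes structurally equivalent, with eight 2-hour FibroQoL sessions to match MBSR, and nothing shows unequal questioning between them.
- That the responder rules are wrong, or that the NNT is the only result shown. An NNT is a measure of benefit, and the same section plans mixed models and Cohen's d with confidence intervals.
- That the Discussion names a worsening peculiar to TAU. It defines the phenomenon as "disappointment among control participants at not receiving treatment", which is not a statement that symptoms worsen.

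**Conclusion.** The point holds in limited form. The adverse-event measure lacks a baseline although two of its three named events are listed disease features, so its reports cannot be sorted from the measure itself into new, worse and pre-existing. If all arms are asked alike, the consequence is dilution: in the illustration, power falls from 0.63 to 0.39 at 13 % background and from 0.30 to 0.09 at 63.8 %. Those figures rest on assumed onset rates and on anxiety-disorder prevalence as a stand-in for reported symptoms, so they show direction and rough scale only.

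Whether TAU is asked is unclear. Any inflation from extra in-treatment enquiries would act against TAU and not between the two programmes. Its size is unknown, and it shrinks towards zero if symptoms persist and TAU is asked at the same visits. Efficacy results are unaffected. The schedule is worth correcting because the remedy is cheap and a missing baseline cannot be filled in later.

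**What to change.** 1. In Table 3, give adverse-event monitoring its own row, separate from MBSR fidelity. Add the checklist at the existing baseline visit and state that all three arms complete it at 2 and 12 months.
2. Count as an adverse event only a symptom that is new or worse than at baseline. The FIQR sleep, anxiety and balance items and the HADS anxiety subscale can support this, and can serve as a fallback for anyone already enrolled without the checklist.
3. Base the between-arm comparison on the visits common to all arms, and list in-treatment reports separately.
4. Optionally, report by arm the proportion with at least a 20 % rise in FIQR total, or with PGIC on the worse side. This uses data already collected.

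The cost is one short extra form at an existing visit, an edit to Table 3 and, if the option is taken, a few table rows. No new visits are needed. The downside is a slightly longer baseline battery.
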